### Statistical analysis

Descriptive statistics will be used to describe the main characteristics of the study population. For the primary research question, data will be analyzed according to the complete case principle. In addition, an intention-to-treat analysis will be performed to explore the robustness of the results. Group differences will be tested using multi-level regression analysis taking into account baseline data on age and gender. The significance level will be adjusted for multiple testing. A dropout analysis will be conducted to control for differential attrition bias. All data analysis will be carried out using SPSS (Version 29, IBM, Armonk, NY, USA).

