### Sample size calculation

The power calculation was based on hypothesis 1. Due to insufficient evidence for the effectiveness of the multidimensional ET feedback, the sample size was calculated based on a minimal clinically important difference of 2.0 points (SD = 2.5 points) between groups in the primary outcome as measured by the BPI [47]. Given a power of 0.9 with a one-sided test and an alpha of 0.05, the calculated total sample size was 66 participants (33 per group). Anticipating a maximum loss to follow-up of about 50%, the calculated target sample size was 132 patients.

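### Complete cases are made the primary analysis, with intention-to-treat only as a check, although the trial allows for loss of up to about half its patients

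*Protocol article*

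**What the plan says.** Protocol article, Statistical analysis: for the primary research question "data will be analyzed according to the complete case principle". The next sentence adds that "an intention-to-treat analysis will be performed to explore the robustness of the results". Group differences are to be tested by multi-level regression that takes account of age and gender. On attrition, the section says: "A dropout analysis will be conducted to control for differential attrition bias".

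Protocol article, Sample size calculation: "Anticipating a maximum loss to follow-up of about 50"%, the evaluable total of 66 is doubled, and "the calculated target sample size was 132 patients".

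Protocol article, Quantitative data collection: T0 and T1 are collected at the clinic during the initial and final examinations. T2 is a questionnaire sent to the patient's home, with a reminder if it has not come back within two weeks. Under the hypotheses in the Background, each comparison applies both at the end of rehabilitation and at the 12-week follow-up.

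**The concern.** This is a choice that the article states, not detail left to a fuller document. If the two analyses disagree, the headline estimate is the one from completers.

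A complete-case comparison is unbiased only if, given the terms in the model, being missing is unrelated to the outcome. The article offers no assumption about why data would be missing and no reason for preferring complete cases. The assumption is hard to take for granted at T2. Return is by post and voluntary, and the outcomes are pain, disability and satisfaction, which may well influence who replies. The intervention also addresses self-regulation and commitment, so reply patterns could differ between arms. The article itself names differential attrition bias as a concern.

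At stake is whether the main answer of a superiority trial keeps the comparability that randomisation created. Recruiting more patients to offset loss keeps the standard error at its planned size; it does not make the remaining patients comparable between arms.

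**Working it through.** **Inputs from the Sample size calculation section.** "minimal clinically important difference of 2.0 points (SD = 2.5 points) between groups"; "Given a power of 0.9 with a one-sided test and an alpha of 0.05"; 33 evaluable patients per group, 66 in total; maximum loss about 50%; target 132.

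**1. The plan's own figures.**
- Inflation for loss: 66 / (1 − 0.50) = 132. This reproduces exactly. In reverse, 132 × (1 − 0.50) = 66 complete cases at the ceiling.
- Base size: n per arm = 2 × (z_α + z_β)² × SD² / Δ². Two-sided at 0.05: 2 × (1.960 + 1.282)² × 2.5² / 2.0² = 32.8, so 33 per arm and 66 in total. One-sided at 0.05, as the text says: 2 × (1.645 + 1.282)² × 2.5² / 2.0² = 26.8, so 27 per arm and 54 in total. The 66 therefore matches a two-sided test. That is a separate matter and does not affect this point.
- Power with 33 per arm is 0.90 two-sided or 0.95 one-sided (normal approximation), so power is protected even at the ceiling.

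**2. Formula for the bias.** In one arm let d be the proportion missing and g the mean outcome of the missing minus that of the observed patients. The mean of the whole arm is the observed mean + d × g, so the complete-case mean is wrong by d × g. The between-arm difference is wrong, in absolute size, by |d_I × g_I − d_C × g_C|, with I for intervention and C for control. It can favour either arm.

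**3. Illustration.** The gaps and arm-specific loss rates below are assumptions; the documents give none. The standard error is that of a simple two-group comparison with SD 2.5: SE = 2.5 × √(2 / n per arm). At 50% loss this is 2.5 × √(2/33) = 0.615.

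With equal loss in both arms and gaps that differ between arms by 1.0 BPI point, the bias is d × 1.0:

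| Loss in each arm | Complete cases of 132 | Bias (BPI points) | SE | Bias / SE |
|---|---|---|---|---|
| 10% | about 119 | 0.1 | 0.459 | 0.2 |
| 20% | about 106 | 0.2 | 0.487 | 0.4 |
| 30% | about 92 | 0.3 | 0.520 | 0.6 |
| 40% | about 79 | 0.4 | 0.562 | 0.7 |
| 50% | 66 | 0.5 | 0.615 | 0.8 |

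- At 50% loss, 0.5 / 2.0 = 25% of the target difference. With no true effect and bias in favour of the intervention, one-sided rejection rises from 5% to 1 − Φ(1.645 − 0.5/0.615), about 20%.
- Unequal loss of 40% and 60% with the same 1.5-point gap in both arms: (0.60 − 0.40) × 1.5 = 0.3 points.
- Equal loss and equal gap in both arms: d × g − d × g = 0, whatever the loss.

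**The case against.** The case for the plan has several parts.

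- **50% is a stated maximum.** A reader might infer that the main answer will rest on half the patients. The article supports only that it may do so at worst. T1 is taken on site after three weeks, and the article gives no split of loss between T1 and T2. Voluntary non-return describes T2, not T1. This stands, and it limits the point.
- **Discarded data.** A reader might infer that patients with T0 and T1 but no T2 are thrown out altogether. The article does not say so. It does not define a complete case, and the term could apply separately at each time point, in which case such a patient still counts at T1.
- **Unused scores.** A reader might infer that T0 and T1 scores play no part in the model. The article names age and gender as covariates, but the multi-level regression may carry the repeated scores as outcomes. The full specification may properly sit in another document.
- **Safeguards exist.** An intention-to-treat analysis and a dropout analysis are both planned. This softens the point but does not answer it: the first is subordinate to the complete-case result, and comparing dropouts with completers describes attrition without removing its bias.
- **The size rests on assumed gaps.** That is correct, and with loss and gap equal in both arms the bias is zero.
- **A mixed model is no cure.** It is valid if data are missing at random. If return at T2 depends on the unseen T2 value itself, it is biased too. This stands and is why the fix includes a delta-adjusted analysis.

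**Conclusion.** The point holds in a limited form. The article gives complete cases precedence over the intention-to-treat analysis while allowing for loss of up to about 50%. At that ceiling the primary result, chiefly at T2, would come from 66 of 132 patients, with power preserved but no corresponding protection against attrition bias.

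How much bias would follow cannot be read from the documents. Under the assumed 1.0-point difference in gaps it runs from 0.1 BPI points at 10% loss to 0.5 points (0.8 standard errors) at 50%, and it is nil when loss and gap are the same in both arms. These figures show what the ordering of the analyses leaves exposed; they do not predict that the trial will be biased. The change is still worth making, because the ordering is fixed in the text, no reason is given for it, and reversing it is cheap.

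**What to change.** Swap the order of the two planned analyses.

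- **Primary:** a likelihood-based mixed model in SPSS on all consented randomised patients as allocated, using every available T1 and T2 value. Terms: group, time, group-by-time, age, gender, and the T0 score where one exists (BPI, NPAD, QuickDASH, RMDQ). The satisfaction measures are taken only at T1 and T2, so their model has no T0 term. A patient with neither a T1 nor a T2 value adds no outcome information; report how many there are in each arm.
- **Sensitivity:** keep complete cases, and define whether that means complete at each time point or at all of them. Add a delta-adjusted analysis for T2 that shifts the imputed values of non-returners over a stated range, separately by arm, because the mixed model assumes missing at random.
- **Wording:** say that the dropout analysis describes differential attrition, not that it controls for it.

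The cost is a rewording of the analysis section and some extra programming in software already named. No new data are needed and the target of 132 does not change. One source of selection remains: the Discussion says that allocation takes place several days before patients are recruited, so selection between allocation and consent is not removed by this change.

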Related to the primary research question, the following hypotheses were developed:In the intervention group, the general subjective treatment outcome measured with the Brief Pain Inventory is on average 2.0 points below the control group at the end of the inpatient rehabilitation program (resp. at 12-week follow-up).The intervention group shows better indication-specific subjective treatment outcomes than the control group at the end of the inpatient rehabilitation program (resp. at 12-week follow-up).The intervention group shows higher levels of satisfaction with rehabilitation than the control group at the end of the inpatient rehabilitation program (resp. at 12-week follow-up).

Additionally, the following secondary research questions concerning the project’s process quality are evaluated by an explanatory approach:How do rehabilitation patients and exercise therapists rate the acceptance and feasibility of multidimensional exercise therapy feedback?What factors influence the patient’s work ability at the end of the inpatient rehabilitation program (resp. at 12-week follow-up)?What are subjective outcome and satisfaction criteria of rehabilitation patients?

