Subjective treatment outcome (generic)	BPI [29, 30]	T0, T1, T2
Subjective treatment outcome (indication-specific)	NPAD [33, 34]	T0, T1, T2
	QuickDASH [35]	T0, T1, T2
	RMDQ [36, 37]	T0, T1, T2
Patient satisfaction	ZUF-8 [38]	T1, T2
	Unstandardized, intervention-specific questionnaire	T1, T2
*Secondary outcome measure*		
Self-regulation competence	Physical activity-related health competence questionnaire (Sub-dimension: self-regulation competence) [42, 43]	T0, T1, T2
*Person-related variables*		
Age, sex, education level, employment situation	Demographic standards [44]	T0
Job profile	GEDA 2019/2020-EHIS [45, 46]	T0
*Process quality measures*		
Acceptance and feasibility of ET feedback	Unstandardized, intervention-specific questionnaire	T1
Work ability	WAS [40, 41]	T0, T1, T2

T0 = Start of inpatient rehabilitation; T1 = End of inpatient rehabilitation; T2 = 12-week follow-up

The short *group ET feedbacks* are provided by the therapist at the end of every shoulder-back school course unit. The shoulder-back school combines educational and exercise components, with the goal of informing patients about anatomy and physiology as well as offering advice on how to prevent and manage pain [9]. It consists of ten course units on consecutive days, each lasting between 30 to 45 min. Every group ET feedback consists of a three-minute evaluation regarding the group’s rehabilitation progress exemplified by the performance, participation and commitment of individual group members.

The *second multidimensional ET feedback* is provided during the final 30-min physical therapy examination at the end of the inpatient rehabilitation program. After an initial interview to determine the patient’s general opinion regarding the program, the assessments and PROMs from the initial examination are repeated to determine the objective and subjective treatment effects. Employing all four levels of ET feedback (Table 2), the therapist then provides the patient with a visual and verbal summary of their performance and individual progress during the inpatient rehabilitation program. Additionally, possibilities for the continuation of training are discussed to facilitate long-term physical activity and social participation following the program.

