### Quantitative data collection

Data related to the primary research question are collected by PROMs at each of the three measurement points (Table 1). The T0 and T1 measurements take place during the respective initial and final physical therapy examinations at the start and end of the three-week inpatient rehabilitation program. The questionnaires for the 12-week follow-up (T2) are sent to the patient’s home, and a reminder is sent if the questionnaires are not returned within two weeks.

In order to test hypothesis 1, the generic subjective treatment outcome is operationalized using the Brief Pain Inventory (BPI) [29, 30]. The BPI measures pain severity as well as pain interference with daily activities. Its rating scales have high construct validity (Factor analysis results: 0.5–0.91) [31] and reasonable internal consistency (Cronbach’s alpha = 0.84) [32]. Furthermore, the BPI shows adequate test–retest reliability (Pearson correlation r = 0.97) [30] and is sensitive to change [31].

For the evaluation of hypothesis 2, indication-specific subjective treatment outcomes are operationalized with the Neck-Pain and Disability Scale (NPAD) [33, 34], the shortened Disabilities of the Arm, Shoulder and Hand Questionnaire (QuickDASH) [35] as well as the Roland and Morris Disability Questionnaire (RMDQ) [36, 37].

Patient satisfaction (hypothesis 3) is evaluated using the ZUF-8 [38], a German version of the Client Satisfaction Questionnaire (CSQ-8) [39] adapted for rehabilitation. In addition, an unstandardized intervention-specific questionnaire is used to assess the patient’s satisfaction with the physical therapy examinations and group ET program (Table 3).

The secondary research questions relating to the project’s process quality are investigated using an unstandardized, intervention-specific questionnaire to evaluate the acceptance and feasibility of multidimensional ET feedback from the patients and therapists’ view. In addition the Work ability score (WAS) [40, 41] is employed to allow for the identification of work-influencing factors of rehabilitation patients using multi-level regression analysis.

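### The group comparison names age and gender as baseline data but never says how the T0 score of the outcome is used; adjusting for it would gain precision at no cost

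*Protocol article*

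**What the plan says.** The protocol article describes the model for the primary research question in one sentence under Statistical analysis: "Group differences will be tested using multi-level regression analysis taking into account baseline data on age and gender". No other section adds a baseline covariate or says what the levels of the model are.

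The T0 scores exist. Quantitative data collection says: "Data related to the primary research question are collected by PROMs at each of the three measurement points". Table 3 gives the schedule for the generic outcome as "Subjective treatment outcome (generic) BPI [29, 30] T0, T1, T2", and the same three time points for NPAD, QuickDASH, RMDQ and the secondary outcome, self-regulation competence. Satisfaction is different: "Patient satisfaction ZUF-8 [38] T1, T2".

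Hypothesis 1, in the Background, is about level and not change: "the general subjective treatment outcome measured with the Brief Pain Inventory is on average 2.0 points below the control group". It is posed for T1 and again for T2. The sample size is framed the same way, on "a minimal clinically important difference of 2.0 points (SD = 2.5 points) between groups in the primary outcome as measured by the BPI". It uses no correlation with baseline.

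**The concern.** The earlier score on the same scale can usually be expected to predict the later score better than age and gender do. A model with group, age and gender therefore leaves in the residual a component of variance that the trial has already measured.

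Two features of this trial add to the interest. The Discussion says that, for operational reasons, allocation is made several days before patients are recruited at the welcoming event. The staff who inform patients there are not blinded, so those who consent may differ between arms. In addition, the main analysis uses complete cases, and the sample size allows for about half of the participants being lost. Either route can produce arms that differ in T0 pain for reasons other than chance, and a comparison of follow-up levels carries part of that difference into the result.

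At stake are the width of the interval around the headline estimate and some protection against imbalance.

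**Working it through.** **Inputs from the protocol article.** Difference 2.0 and SD 2.5 on the BPI, power 0.9, alpha 0.05 one-sided, 33 per group after losses, 132 recruited (Sample size calculation). Allocation 1:1 (Setting and participants).

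**Assumptions.** The article does not give the correlation r between T0 and follow-up BPI. I take 0.3, 0.5 and 0.7. The 0.97 in Quantitative data collection is test-retest reliability and is not this quantity. I take the T0 SD as 2.5, equal to the planning SD, and ignore any variance explained by age and gender.

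**The plan's own figure.** By the normal approximation, n per group = 2 × [2.5 × (z_alpha + z_power) / 2.0]².
- Two-sided 0.05: 2 × [2.5 × (1.960 + 1.282) / 2.0]² = 32.8, so 33 per group and 66 in total, as stated. Then 66 / (1 − 0.5) = 132, also as stated.
- One-sided 0.05: 2 × [2.5 × (1.645 + 1.282) / 2.0]² = 26.8, so 27 per group and 54 in total.

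The stated number thus fits a two-sided test, while the text says "Given a power of 0.9 with a one-sided test and an alpha of 0.05". That needs reconciling separately; here I show both.

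**Precision with and without T0.**
- Residual SD = 2.5 × √(1 − r²)
- SE of the group difference = residual SD × √(2/33), where √(2/33) = 0.246
- Power from the noncentral t distribution with noncentrality 2.0 / SE and 63 to 64 degrees of freedom

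| r (assumed) | Residual SD | SE | Power, one-sided 0.05 | Power, two-sided 0.05 |
|---|---|---|---|---|
| no T0 | 2.50 | 0.615 | 0.94 | 0.89 |
| 0.3 | 2.39 | 0.587 | 0.96 | 0.92 |
| 0.5 | 2.17 | 0.533 | 0.98 | 0.96 |
| 0.7 | 1.79 | 0.440 | 0.998 | 0.99 |

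Residual variance falls by r², that is by 9%, 25% or 49%.

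**Carry-over of a T0 difference.** With equal SDs, a T0 difference of D points between arms shifts the unadjusted comparison of follow-up levels by r × D. For scale, the 95% range of D by chance alone is 1.96 × 2.5 × 0.246 = ±1.21 points, so r × D reaches 0.36, 0.60 or 0.84 points, against a target of 2.0. This chance part is already contained in the SE of 0.615 and is not an additional error. A T0 difference caused by selection or by unequal loss is not contained in it, and the documents give no basis for its size.

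**The case against.** The strongest reply is that the sentence specifies a multi-level regression. With one centre and three measuring points, occasions within patients is a natural level structure. T0 would then be part of the response, a group-by-time contrast would use it, and listing only age and gender as covariates would be normal. The article is also a condensed account that does not call its covariate list complete. This stands to the extent that the text cannot be read as ruling T0 out. But closed course groups, mentioned in the Discussion, could equally be the level, and hypothesis 1 is worded as a difference in level. A reader cannot tell which was meant.

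The choice of contrast also matters. A group-by-time contrast with freely estimated T0 means amounts to comparing changes, with SE = 2.5 × √(2(1 − r)) × 0.246. That is 0.73, 0.62 or 0.48 at r = 0.3, 0.5 or 0.7, which is worse than the unadjusted 0.615 at r = 0.3 and no better at 0.5. Saying only that T0 is in the response would therefore not settle the point.

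A second reply is that the trial does not need the gain. At the stated one-sided 0.05, 33 per arm already give power of 0.94. This stands for the unadjusted alpha. The plan also adjusts the significance level for multiple testing, so the extra precision is not idle.

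A reader might infer that the planned test is invalid, biased or underpowered. The documents do not support that: under sound randomisation the comparison without T0 is unbiased and its SE already reflects chance imbalance. A reader might also infer that T0 adjustment cures allocation before recruitment or complete-case attrition. It does not; it removes only the part of an imbalance that the T0 score captures. The plan separately provides an intention-to-treat analysis and a dropout analysis.

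**Conclusion.** The point holds as a recommended improvement for hypotheses 1 and 2 and for self-regulation competence. The article names two baseline variables, is silent on the T0 outcome score that it collects, and so leaves the use of the baseline open. If T0 is not used, the variance of the estimate is larger by a factor 1/(1 − r²): 1/0.91 = 1.10, 1/0.75 = 1.33 or 1/0.51 = 1.96 for the assumed correlations. A non-chance T0 imbalance would also enter in proportion r.

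The size rests on the assumed r, which may differ between T1 and T2 and between instruments, on equal SDs, and on 33 completers per arm. The direction does not depend on the exact value: any appreciable correlation gives a gain. Hypothesis 3 lies outside the point, because ZUF-8 and the intervention-specific satisfaction questionnaire have no T0 value.

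**What to change.** Extend the model sentence under Statistical analysis: for BPI, NPAD, QuickDASH, RMDQ and self-regulation competence, the T0 score of the same instrument enters as a covariate, besides age and gender, with group differences estimated at T1 and at T2.

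If T0 was meant to be a repeated response, say so, and state the levels of the model and the contrast at T1 and T2 that uses the baseline. Constraining the T0 means to be equal across arms keeps the precision of covariate adjustment but presumes comparable arms at T0. Given allocation before recruitment, the covariate form is the simpler choice.

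The T0 score should be one completed before the first feedback. The Intervention section describes that order for the indication-specific measures; the same should be confirmed for the BPI. No T0 substitute is needed for the satisfaction measures.

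The cost is a sentence or two, settled before outcome data are analysed. It needs no new data and no change to the sample size.

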**Methods:**

The study is designed as a prospective, mono-centric, randomized controlled, superiority trial (RCT) with two parallel groups and three measuring points: T0 = start of three-week inpatient rehabilitation, T1 = end of three-week inpatient rehabilitation, T2 = 12-week follow-up. In total, 132 patients suffering from chronic neck, shoulder and/or lumbar spine disorders will be recruited. The intervention involves multidimensional exercise therapy feedbacks during the initial and final physical therapist examination, as well as short exercise therapy feedbacks during the course units of the mandatory group-based exercise therapy program. Primary outcomes are the subjective treatment outcome, assessed by BPI and indication-specific questionnaires, as well as patient satisfaction, assessed by ZUF-8 and an intervention-specific questionnaire. The final data collection is expected by May 2023.

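### The sample size makes no allowance for the promised multiplicity adjustment; if alpha is split over three or more primary tests, 33 per group does not give the stated power of 0.9

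*Protocol article*

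**What the plan says.** - **Sizing.** The Sample size calculation section bases the size on hypothesis 1 only. It assumes a "minimal clinically important difference of 2.0 points (SD = 2.5 points) between groups" on the BPI. "Given a power of 0.9 with a one-sided test and an alpha of 0.05", it arrives at 66 evaluable patients (33 per group), doubled to 132 for a maximum loss of about 50%. No multiplicity allowance is mentioned.
- **Analysis.** The Statistical analysis section states: "The significance level will be adjusted for multiple testing". It names neither a procedure nor the set of tests concerned. The main analysis uses complete cases.
- **Primary outcomes.** The abstract says: "Primary outcomes are the subjective treatment outcome, assessed by BPI and indication-specific questionnaires, as well as patient satisfaction". Table 3 lists six instruments under the primary heading: BPI, NPAD, QuickDASH, RMDQ, ZUF-8 and an intervention-specific questionnaire. All six are collected at T1 and T2.
- **Time points.** Each of the three hypotheses in the Background is worded for both occasions: "at the end of the inpatient rehabilitation program (resp. at 12-week follow-up".
- **BPI score.** The Quantitative data collection section notes: "The BPI measures pain severity as well as pain interference with daily activities". The sizing does not say which of these scores, or which time point, its 2.0 and 2.5 refer to.

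**The concern.** Power of 0.9 is claimed for a BPI test carried out at 0.05. If the analysis lowers that level because other primary outcomes share the error rate, the BPI test is run at a stricter level than the one it was sized for, and the only powered hypothesis has less power than claimed. The protocol gives no order of testing that would protect the BPI. Basing the size on hypothesis 1 does not by itself make it the first test in a sequence, and T1 and T2 are not ranked either. A trial that misses on the BPI could then have missed because of how alpha was shared rather than because the intervention does not work, and the protocol's power statement would not reveal this.

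**Working it through.** **Inputs** (Sample size calculation section): difference 2.0, SD 2.5, so d = 2.0/2.5 = 0.8; alpha 0.05; power 0.9; 33 evaluable per group.

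**Step 1: reproduce 33 per group.** Normal approximation, n per group = 2(z_alpha + z_0.90)² / d².
- One-sided 0.05: 2(1.645 + 1.282)² / 0.64 = 26.8, so 27 (28 by the noncentral t), a total of 54 to 56.
- Two-sided 0.05: 2(1.960 + 1.282)² / 0.64 = 32.8, so 33 (34 by the noncentral t), a total of 66.

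The stated 66 is therefore the two-sided 0.05 result (equivalently one-sided 0.025), not the stated one-sided 0.05 result. The inflation reproduces: 66 / (1 − 0.5) = 132.

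**Step 2: power at 33 per group if alpha is split.** *Assumption:* Bonferroni, 0.05/k per test, because the protocol names no method. Two-sample t-test with 64 degrees of freedom and noncentrality 0.8 × √(33/2) = 3.25. Power is the probability that this noncentral t exceeds the critical value for 0.05/k (one-sided) or 0.05/(2k) (two-sided).

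| Tests k | 0.05/k | Power, one-sided | Power, two-sided | n per group for 0.90 (one-/two-sided) |
|---|---|---|---|---|
| 1 | 0.0500 | 0.94 | 0.89 | 28 / 34 |
| 2 | 0.0250 | 0.89 | 0.83 | 34 / 41 |
| 3 | 0.0167 | 0.86 | 0.78 | 38 / 44 |
| 6 | 0.0083 | 0.78 | 0.70 | 44 / 50 |
| 12 | 0.0042 | 0.70 | 0.61 | 50 / 56 |

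The values of k correspond to possible families: 2 is the BPI at T1 and T2; 3 is one test per hypothesis; 6 is one test per instrument; 12 is six instruments at two time points.

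**Step 3: dependence on loss.** The figure of 33 per group is what remains of 66 randomized per group after the maximum 50% loss. With no loss, power at k = 12 is 0.97 one-sided and 0.95 two-sided. The 50 or 56 per group needed at k = 12 would be reached if loss stayed at or below 1 − 50/66 = 24% or 1 − 56/66 = 15%.

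**The case against.** **The two statements can coexist.** A reader might infer that an alpha of 0.05 in the sizing and an adjusted level in the analysis contradict each other outright. The documents do not support that. A fixed sequence that opens with one BPI test controls the error rate and still tests the BPI at the full 0.05. An article may leave the procedure to the full plan, so the absence of a named method is not the fault here. This stands, and it makes the loss of power conditional on a split.

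**The twelve-test family is not stated.** Nothing says that every instrument and both time points share one alpha. With a family of two, one-sided power is 0.89, essentially as claimed; one-sided 0.05/2 even reproduces 33 per group. But the sizing states 0.05 and mentions no such allowance, so that explanation cannot be read into it. Bonferroni also ignores correlation between outcomes, and Holm would lose no more power. The table is therefore an upper bound on the loss.

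**Loss may be smaller than 50%.** T1 is measured in the clinic and only T2 is postal, and no loss figure is given for T1 separately. This also stands. But 0.9 is claimed for 33 per group, and with a complete-case main analysis that evaluable number is the one that counts.

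**Family-wise error.** A reader might infer that the trial runs many primary tests at an uncorrected 5%. It does not: the Statistical analysis section commits to an adjustment, so an inflated error rate would describe a trial that departs from its own plan.

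**Conclusion.** The mismatch is real, but its effect is conditional. The sizing uses an unadjusted 0.05 for one hypothesis and allows nothing for the adjustment announced for the analysis. If alpha is split over three or more primary tests, the stated 0.9 is not reached at 33 per group under either sidedness: it is 0.86 or 0.78 at three tests, down to 0.70 or 0.61 at twelve. With two tests it is nearly kept one-sided (0.89) but not two-sided (0.83).

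These figures assume Bonferroni, d = 0.8, a two-sample comparison of means and the maximum 50% loss. They would improve with a less conservative method or better retention, and a fixed sequence led by the BPI would remove the loss for that test.

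One finding needs no assumption about the adjustment: under that same comparison of means, the stated one-sided 0.05 does not yield 33 per group, whereas two-sided 0.05 does.

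**What to change.** In the Statistical analysis section, replace the general sentence on adjustment with a stated order of testing:

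1. The one BPI score and the one time point to which the 2.0 and 2.5 figures refer, tested at the full alpha used for sizing.
2. The same BPI score at the other time point.
3. The indication-specific outcomes, then ZUF-8, in a fixed order at the same level, each tested only if the preceding test succeeds.

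State also whether the intervention-specific questionnaire has a place in this order or stands outside it.

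Alternatively, keep an alpha split, define its family and procedure, and restate in the Sample size calculation section the power at the adjusted level. If 0.9 is to be kept under a twelve-way Bonferroni split, that means 50 (one-sided) or 56 (two-sided) evaluable per group.

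In either case, correct the sidedness so that the stated test and alpha produce 33 per group.

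The first option costs only wording, fixed before the data are analyzed, with no added patients or visits. Its price is that if the first BPI test fails, all later hypotheses become descriptive. The second option means either accepting a lower stated power or, to keep 0.9, having more evaluable patients.
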